### **2.3.10 Power and sample size considerations**

For sample size calculation, we consider the intra-cluster correlation coefficient, the number of events, the expected effect, and the power of the study. Based on pilot data in this patient population, we expect that 30% of patients in the usual care control will have a DNR code status, which will increase to 45% in the intervention group. We plan to include 174 residents (cluster) with a mean of 5 eligible patients per week over a 3-week period (total of 15 patients per cluster) in the five participating centers over a total study time of 2 years. Based on these assumptions, we will include 2610 patients among 174 residents, which will give this study an 80% power at a 0.05 alpha error with an inter-cluster correlation of 0.5. Because the inter-cluster correlation in this setting is unknown, we used a conservative estimate above, but plan to possibly adjust the sample size based on a blinded interim analysis after data of 30 residents (cluster) is collected. In this interim analysis, we estimate the intraclass correlation of code status decisions, i.e., how much the code status decisions are cluster-dependent. Based on this estimation of intraclass correlation, we will adjust the total required sample size.

### **2.3.11 Recruitment and recruitment feasibility**

To achieve our calculated sample size of 174 residents, each included for a 3-week period, in the five centers, we plan to include 2-3 residents in parallel (totaling to 35-53 residents per year per center). All centers have between 20-60 residents per year, which stay at a center for 1-3 years. Thus, due to rotation we expect to have between 30 and 90 eligible residents per center per year. We will include centers stepwise. In case, one or more centers fall short of recruitment, we plan to increase the time for recruitment in the other centers until our sample size goals are reached.

Strategies to achieve the estimated inclusion rate will include:

## *Study protocol and statistical analysis plan*

- (1) A close monitoring of recruitment rates with monthly visits of study sites by one member of our study team will help to facilitate recruitment and remove potential barriers.
- (2) Each center will receive a contact list with the mobile numbers of the study coordinator and the principal investigator to enable support and clarification in situations, in which local investigators might be unsure, whether to recruit a patient.
- (3) Monthly newsletters and alerts will be sent to participating centers indicating the actual progress of the study.
- (4) Monthly investigator meetings will be held to exchange experiences, discuss processes and problems to guarantee an uniform approach between all participating study sites.
- (5) Quarterly information meetings will be held in all participating hospitals to inform healthcare providers about the ongoing study.

We have successfully used these approaches in a currently recruiting multicenter randomized trial supported by the Swiss National Foundation (SNF 10531C\_182422) investigating the effects of ward-rounds on patients' perception of quality of care (<http://clinicaltrials.gov/ct2/show/NCT03210987>).

To make a reasonable estimate of included residents and eventually recruited patients in our study, we chose a stepwise approach: First, we obtained the total number of residents working on ward-based medicine responsible for admissions. Second, the annual report of each participating center provides us the number of hospitalized patients that enable us to make a sound estimation of potentially eligible patients. All participating centers currently have between 4220 and 8000 hospitalized patients annually.

### **2.3.12 Potential limitations**

We expect heterogeneity regarding our patient population. However, we decided against excluding any patient based on the type of illness and comorbidity in order to obtain a representative population of medical patient in Swiss hospitals.

## **2.4 Parallel study: Code status discussions in patients with futility regarding CPR**

Cardiopulmonary resuscitation (CPR) is a medical invasive treatment in case of a cardiac arrest. The Swiss Academy for Medical Sciences recommends that healthcare providers start resuscitation attempts if there is a chance for the patient to survive a cardiac arrest without severe neurologic deficits, unless a “do not resuscitate” (DNR) code status is present. In contrast, for patients with terminal illness CPR may not always be appropriate. Outcome after in-hospital cardiac arrest is generally poor with a survival rate of approximately 20% and many survivors subsequently suffer from permanent brain damage or disability[23, 24]. Certain pre-existing medical conditions such as cancer, renal failure, sepsis or pulmonary diseases are associated with even worse outcomes. This raises the question of futility regarding resuscitation measures[51, 52]. In this context, medical futility may be defined as a judgment that further medical treatment of a patient would have no useful result, or that a medical treatment whose success is possible although reasoning and experience suggest that it is highly improbable.

## *Study protocol and statistical analysis plan*

In some countries including Switzerland, physicians are allowed to put a unilateral DNR in place in case resuscitation measures are judged as futile[53, 54]. In line with this, the American Heart Association Guidelines state that withholding CPR is ethically justified if functional survival of patients is highly unlikely[55]. However, there is no universally accepted method to assess futility. In clinical practice, evaluation of futility is mainly based on the clinician's judgement and patient characteristics such as age and comorbidities.

Recently Ebell et al developed the GO-FAR score, a clinical risk score to predict the estimated likelihood of neurologically intact survival of patients after in-hospital resuscitation[41]. The authors developed a multivariate prediction model based on 51`240 patients who experienced in-hospital cardiac arrest and calculated cut-off scores indicating likelihood of functional survival. The two lowest categories represent very low (<1%) and low (1-3%) likelihood of survival. It has therefore been suggested that these patients should be considered futile regarding CPR attempts [42]. Another tool to assess whether patients are at increased risk for poor outcome is the Clinical Frailty Scale[43]. This 9-category scale combines cognitive and physical aspects of frailty such as comorbidity, cognitive impairment and disability. Research has shown that the scale, which is increasingly used in routine screening of older patients, predicts short-term mortality[44, 45]. However, the prevalence of futility in hospitalized patients upon admission assessed through the GO-FAR score and the Clinical Frailty Scale has not been systematically investigated.

According to the literature, futility may be defined as a GO-FAR score  $\geq 14$  or patients in categories 7-9 in the Clinical frailty scale. In 2012, a British multi-center cohort study assessed medical charts of cardiac arrest patients, in which resuscitation attempts had been performed[26]. In more than 3 of 4 patients the code status was unknown and 67% of patients that were resuscitated, had an underlying pre-existing fatal disease. An independent post-hoc assessment of all cases found that a DNR status would have been appropriate in 85% of cases, because resuscitation attempts were judged to be futile and thus CPR had little chance to be beneficial, but high risk to prolong the dying process[56].

However, informing a patient that resuscitation measures in case of a cardiac arrest are judged as futile and setting a DNR status is complex and challenging. Due to their limited experience in code status discussion, this might be especially true for unexperienced medical residents.

In this ancillary project we aim to examine, whether a communication workshop and a checklist for communication about futility is associated with a higher rate of DNR code status in patients who are considered futile according to either the Go-Far Score or the Clinical Frailty Scale.

### *Interventions of the parallel project*

Patients, in whom resuscitation attempts are considered futile defined as a Go-Far score  $\geq 14$  or patients in categories 7-9 in the Clinical frailty scale, will be included in this ancillary project. Similar to the main project, code status discussions will take place upon admission of patients. Residents allocated to the intervention

## *Study protocol and statistical analysis plan*

group will participate in the above mentioned communication workshop for the main project. During the workshops, residents will also receive detailed instructions about communication strategies in patients with futility. Additionally, residents in the intervention group will be given a checklist for communication of futility (Appendix). To reduce bias, medical residents in the control group will also receive information about the importance of code status discussions and general communication training, but no teaching regarding communication of futility.

### Outcomes in parallel project

The parallel project is designed to investigate whether checklist-guided communication of futility increases the rate of DNR code status. The primary outcome is thus the frequency of DNR code status among patients per resident.

Secondary outcomes are defined as follows:

#### 1. Patient-associated outcomes

- a) Patients' trust in the treating physician assessed through the validated German translation of the Trust in Physician Scale[57].
- b) Patients' psychological burden assessed by the validated German translation of the Hospital Anxiety and Depression Scale (HADS)[58].
- c) Patients' concerns and fears assessed by the validated German translation of the State-Trait Anxiety Inventory[59]
- d) Patients' concerns and fears brought up by the resuscitation discussion: Specifically, we will assess the following dimensions: (1) disturbance caused by the discussion, (2) fear of suffering from an actual cardiac arrest, (3) fear of suffering from a life-threatening disease (4) perceived feeling of being put under pressure during discussion; each of them rated on a VAS (0-10).
- e) Patients' satisfaction and perceived overall quality of the code status discussions: Specifically, we will focus on the following dimensions, each rated on a VAS (0-10): (1) overall satisfaction with resuscitation discussion; (2) perceived transparency of the discussion; (3) comprehensibility of the medical information regarding a resuscitation process and measures; (4) clarity of the medical information regarding a resuscitation process and measures; (5) how well patients' questions were answered; (6) agreement with the decision of putting a DNR code status in place; (7) perceived competence of the medical team; (8) perceived listening skills of the physician;

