**2.3.9 Statistical approach**

The primary analysis population is the full analysis set, which, following intention-to treat (ITT) principles, includes all randomized patients.

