## *Study protocol and statistical analysis plan*

We will use cluster specific methods because residents rather than patients are randomized, and we expected that variance in how patients are managed would be partly explained by the resident. We will further account for the level of the participating center (hospital), as DNR discussions may vary according to study center. For each of the outcome measures we will test the null hypothesis that the likelihood of the outcome is the same in both study groups after accounting for some baseline characteristics (i.e., age, gender, main medical diagnosis). We will use hierarchical logistic regression to test for an effect of the intervention on any binary outcome measures and linear regression for any continuous outcome measure.

All analyses will be conducted using Stata. All analyses were performed using STATA 15.1 (Stata Corp, College Station, TX). For all analyses, we accept a type I error rate of  $\alpha = 5\%$ .

The design of our study and statistical approach was developed in close collaboration with statisticians and epidemiologists of the Clinical Trial Unit (CTU) of the University Hospital Basel.

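### Parallel project: agreement with a DNR decision has a clear meaning only where a DNR was set, so testing it between arms can compare groups formed by the primary outcome

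*Combined protocol and SAP*

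**What the plan says.** The parallel project enrols on futility alone: "Patients, in whom resuscitation attempts are considered futile defined as a Go-Far score" at or above the stated cut-off, or in the stated frailty categories (section 2.4, Interventions of the parallel project). Enrolment does not depend on the code status that results.

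Its aim is to "investigate whether checklist-guided communication of futility increases the rate of DNR code status", and "The primary outcome is thus the frequency of DNR code status among patients per resident" (Outcomes in parallel project).

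Among the patient-associated secondary outcomes, group e) lists eight dimensions of satisfaction and perceived quality, each on a 0–10 VAS. The sixth is "6) agreement with the decision of putting a DNR code status in place". No subgroup is named for it, and nothing says how a patient without a DNR should answer. The background to section 2.4 adds that in some countries, including Switzerland, "physicians are allowed to put a unilateral DNR in place in case resuscitation measures are judged as futile".

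The parallel project has no statistical section of its own. The general one (2.3.9) states: "The primary analysis population is the full analysis set, which, following intention-to treat (ITT) principles, includes all randomized patients". It plans a test of no difference between groups for each outcome measure, adjusted for age, gender and main diagnosis, with "linear regression for any continuous outcome measure". It gives no separate analysis set, missing-data rule or method for an item whose meaning depends on code status.

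**The concern.** Read naturally, the item asks about a decision that was taken for some patients and not for others. Which patients those are is settled after randomisation, by the very process the intervention is meant to change. If the intervention works as hoped, DNR patients in the intervention arm will include some who would have stayed full code under usual care. DNR patients in the two arms are then different kinds of patient, and randomisation no longer protects a comparison between them. Adjusting for age, gender and main diagnosis removes only the part of that difference that those three variables explain.

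The item matters because it is the most direct patient-rated measure of whether patients accept the DNR orders that the project hopes to make more frequent. A difference produced by selection could be read as harm or as benefit, and a real effect could be masked.

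**Working it through.** **Figures in the plan.** The documents give no sample size, DNR rate or power for the parallel project, so there is no figure of its own to reproduce. The main trial's calculation (section 2.3.10) does reproduce: 30% vs 45%, two-sided 0.05 and 80% power need 163 per arm; the design effect is 1 + (15 − 1) × 0.5 = 8; 163 × 8 = 1304 per arm; 1304 / 15 rounds up to 87 clusters per arm, hence 174 residents and 2610 patients. It does not bear on this point. The main trial excludes futile patients, so its 30% and 45% cannot be carried over.

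**Logic.**
1. Enrolment is by futility, whatever code status follows.
2. DNR frequency is the primary outcome, so some patients are expected to have no DNR.
3. The project is "designed to investigate whether checklist-guided communication of futility increases the rate of DNR code status", so the share with a DNR is hypothesised to differ by arm.
4. Section 2.3.9 applies a between-arm test to each outcome measure.
5. If only DNR patients give a value, that test is made in a subgroup defined by the primary outcome.

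**Size: a direct identity.** Suppose everyone who would be DNR under usual care would also be DNR under the intervention, and no patient's agreement changes. With DNR rates p0 (control) and p1 (intervention), the arm difference among DNR patients is

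(p1 − p0) / p1 × (mean rating of the additional DNR patients − mean rating of the others).

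At an assumed 60% vs 75% the multiplier is 15/75 = 0.20, so each point by which the additional patients rate lower or higher shifts the arm difference by 0.2 points. The sign follows the additional patients.

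**Size: a threshold model (all inputs assumed).** A DNR is set when a latent acceptance score, standard normal, exceeds a cut-off c giving rate p. Agreement correlates ρ with acceptance, and the intervention has no effect on agreement. With φ the standard normal density, the difference among DNR patients, in SD units, is

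ρ × [φ(c1)/p1 − φ(c0)/p0].

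Example, 60% vs 75%: φ(c0)/p0 = 0.386/0.60 = 0.644; φ(c1)/p1 = 0.318/0.75 = 0.424; the bracket is −0.220; with ρ = 0.5 the difference is −0.110 SD.

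| Assumed DNR, control vs intervention | Without a value, control / intervention | Ratio of denominators | Difference in SD at ρ = 0.3 / 0.5 / 0.7 | VAS points at assumed SD 2.5 |
|---|---|---|---|---|
| 50% vs 65% | 50% / 35% | 1.30 | −0.068 / −0.114 / −0.160 | −0.17 / −0.29 / −0.40 |
| 60% vs 75% | 40% / 25% | 1.25 | −0.066 / −0.110 / −0.154 | −0.17 / −0.28 / −0.39 |
| 70% vs 85% | 30% / 15% | 1.21 | −0.067 / −0.111 / −0.156 | −0.17 / −0.28 / −0.39 |
| 80% vs 90% | 20% / 10% | 1.12 | −0.046 / −0.077 / −0.108 | −0.12 / −0.19 / −0.27 |
| 50% vs 50% | 50% / 50% | 1.00 | 0 / 0 / 0 | 0 / 0 / 0 |

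The minus sign comes from assuming ρ > 0. The formula is linear in ρ, so a negative ρ gives the mirror image.

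**The case against.** **The restriction is inferred.** A reader might infer that the item exists only for patients given a DNR and that the arms are therefore not comparable. The documents do not say so. No subgroup is named, and the questionnaire's wording and routing are not shown. Every patient in the project is judged futile, so one who refused a proposed DNR could sensibly rate low agreement. This stands, and the conclusion has to be conditional. It does not settle the matter: put to everyone as worded, the item asks a full-code patient about a decision that was not taken and perhaps never raised, and the plan does not say whether that patient leaves it blank or what an answer would mean.

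**The direction is unknown.** A reader might also infer that the additional DNR patients are the reluctant ones, so that the bias runs against the intervention. Nothing in the documents supports that. Section 2.1 cites a cancer study in which code status was often presumed without discussion and almost a third of patients presumed full code would have preferred DNR. Such patients could agree strongly once asked.

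**The stakes are limited.** Trust, the anxiety and depression scales, feeling put under pressure, overall satisfaction and the physician's perception of patient agreement do not require a DNR to be set. This stands. A harm would not have to be detected through this item alone.

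**Rewording changes the construct.** Agreement with whichever code status was documented pools acceptance of DNR with acceptance of full code. This also stands, and is why the DNR-only result should be kept as description.

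**Conclusion.** The point holds in conditional form. As worded, the item has a clear referent only where a DNR was set, and the only stated analysis rule would test it between arms. If only DNR patients give a value, the comparison conditions on the project's primary outcome and can show a difference, in either direction, without any true effect on agreement.

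The bias needs three things: values from DNR patients only, a difference between arms in who receives a DNR, and a link between DNR setting and agreement. With gaps of 10 to 15 points and correlations of 0.3 to 0.7 it is about 0.05 to 0.16 SD, or about 0.1 to 0.4 VAS points at an SD of 2.5. The DNR rates, correlation and SD are all assumptions, so the true size is unknown. With equal rates under the same model it is zero.

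The scope is one of eight dimensions in one secondary outcome group of an ancillary project. Neither primary outcome nor the sample size is affected. The change should still be made, because the stated analysis rule, applied to this item on its natural reading, gives up the protection of randomisation and the remedy is cheap.

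**What to change.** 1. For the between-arm comparison, use an item that every patient in both arms can answer, for example agreement with the code status documented for me, and analyse all patients who complete the questionnaire in the arm of their resident.
2. Keep the DNR-agreement item as a description among patients with a DNR. Give the number with a DNR and the number answering in each arm, with no between-arm test and no causal claim.
3. State both rules in the outcome list of the parallel project and in section 2.3.9.

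If data are already collected, only the second step, and the sentence recording it, applies.

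The cost is one questionnaire item and a line or two of text, with no extra patients or visits. The downside is that the all-patient item measures agreement with the code status decision in general, not acceptance of a DNR specifically. The descriptive DNR-only result keeps that information available.

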#### Physician-associated outcomes

## *Study protocol and statistical analysis plan*

- a) Physicians' perception of the resuscitation discussion: Specifically, perceptions will be assessed for both study groups separately in regard to the following dimensions; each rated on a VAS (0-10):  
(1) satisfaction with resuscitation discussion and self-confidence during the discussion; (2) perceived time management of the discussion, (3) physicians' perceived understanding and concerns of patients, (4) physicians' perception of patient indecisiveness and agreement
- b) Surprise question to identify patients at risk of death within the next 12 months

After 30 days we will assess length of hospital stay, ICU admissions, if any changes in code status occurred, in-hospital resuscitations, code status violations and in-hospital deaths through medical chart review.

### **2.5 Relevance and impact**

Proactive involvement of patients into the decision process is an important part of patient-centered care. Still, few randomized controlled studies have focused on the best approach to conduct codes status discussions. Herein, we propose the first large-scale multicenter trial that will give important, new insights on the effect of checklist-guided shared decision-making on patients' choice for DNR and decisional comfort with their choice as well as on other patient- and healthcare-relevant outcomes. Considering different dimensions of quality of care such as patients' understanding will help to realize a more patient-centered medicine by enabling well-informed patients to take part in a shared decision-making process.

